#### Antibiotics

Antibiotics are used to treat diagnosed *S*. Paratyphi A infection or at day 14 postchallenge for those who have not been diagnosed.

The first line antibiotic will be oral ciprofloxacin 500 mg two times a day for 7 days, in-line with guidance on enteric fever treatment.^21^ In fully susceptible *S*. Typhi isolates ciprofloxacin was shown to shorten time to resolution of symptoms, fever clearance time and bacteraemia when compared with azithromycin.^22^ Participants will be given verbal and written information regarding the possible side effects of ciprofloxacin use. For any participant in whom a contraindication to these first line antibiotics becomes apparent oral trimethoprim/sulfamethoxazole, oral azithromycin or oral amoxicillin will be used as second-line therapy.

#### Other trial interventions

Concomitant medication can be provided for symptomatic control of paratyphoid infection, before and after diagnosis. Concomitant medication after paratyphoid diagnosis includes antibiotics and antipyretics if required (online supplemental material 8).

10.1136/bmjopen-2022-068966.supp8Supplementary data

## Sample size

Based on findings from the previous challenge studies performed at OVG, the assumption of attack rate of 58% was used in the control group.^14 15^ To demonstrate a protective effect of 70% (ie, 30% relative risk in attacking rate), resulting in a reduction in attack rate from 58% in the control group to 17.4% in the vaccine group, 33 participants would be needed per group to achieve 90% power (1−β) at two-sided 5% significance level (α).

We observed less than a 10% of dropout rate from previous vaccine trial using typhoid challenge model.^12^ The sample size will be inflated to 37–38 participants per group to account for at least a 10% dropout. We expect to randomise 74–76 participants in total.

## Statistical analysis

The analysis of the primary end point will be a calculation of the proportion of participants diagnosed with paratyphoid fever in the CVD 1902 group relative to the placebo group. The proportion of participants diagnosed with paratyphoid fever (ie, the attack rate) and the associated 95% CIs will be presented by group at day 28 after challenge. When calculating paratyphoid diagnosis proportions, the numerator will be the number of participants who meet the criteria for diagnosis and the denominator will be the per protocol population. The difference in proportions between the CVD 1902 and placebo groups will be analysed using Pearson’s χ^2^ test (or Fisher’s exact test if expected counts in any group are less than 5). To fulfil the primary objective, the protective effect of CVD 1902 over placebo will be calculated by:

PE=100×(AR_Placebo_–AR_CVD 1902_)/AR_Placebo_=100×(1–AR_CVD 1902_/AR_Placebo_),

Where PE is the protective effect and AR is the attack rate.

Time-to-event analyses of individual components of the primary outcome (positive blood culture and oral temperature ≥38.0°C) will be conducted using the Kaplan-Meier method and will include all participants. Participants not meeting the criteria for an individual component of the primary endpoint will be censored in the analysis at the final monitoring for those undiagnosed. Participants who withdrew or had potential interference with vaccine effect or infection challenge (eg, treated prior to day 14 with no diagnosis of paratyphoid) will be censored in the analysis at the time of withdrawal or interference.

Immunogenicity data are expected to be highly skewed and will be log-transformed prior to analysis. Results will be presented as geometric means with 95% CIs. Values below the limit of detection (LLOD) will be imputed with half the value of the LLOD.

## Ethics and dissemination

### Ethical approval, regulation and governance

Ethical approval for this study has been obtained from the Berkshire Research Ethics Committee and Health Research Authority (REC reference: 21/SC/0330) and the study will run in accordance with the ethical principles of the Declaration of Helsinki.

The use of an unlicensed vaccine in this study, CVD 1902, is regulated by the Medicines for Human Use (Clinical Trials) Regulations 2004 (Medicines and Healthcare products Regulatory Agency (MHRA)). As CVD 1902 is a genetically modified organism, relevant approvals have been obtained for its use in this study from the Department of Environment, Food and Rural Affairs, Oxford University Hospitals NHS Foundation Trust and the Centre for Clinical Vaccinology and Tropical Medicine. The challenge agent falls outside the remit of these regulators and therefore is judged according to common law and best practice.^23^ Regional ethics committees therefore provide support in governing challenge studies.

An independent DSMC consisting of an experienced group of infectious disease clinicians, scientists and a statistician will be appointed to provide real-time oversight of safety and trial conduct. The DSMC will review safety data collated from the electronic CRFs (eCRFs) and e-diaries including solicited and unsolicited symptoms, laboratory results and vital signs. Following prime vaccination of a sentinel group of six participants relevant safety data will be reviewed by the DSMC. If there are no safety concerns these participants can proceed to their second vaccination and further participants can begin vaccination. Further DSMC reviews will occur regularly throughout the trial.

A development safety update report for the investigational medicinal product will be prepared annually, on the anniversary of the MHRA approval for the trial.

### Risks

The general risks to participants in this study are associated with potential side effects from the vaccine or placebo, symptomatic infection following challenge and the small risk of subsequent complications from paratyphoid infection. Additionally, there is a small risk of secondary transmission of *S*. Paratyphi A to close contacts of participants. The university has a specialist insurance policy in place, which would operate in the event of any participant suffering harm as a result of their involvement in the research.

#### Vaccine

In the phase I trial ‘CVD 1902 was well tolerated without clinically significant adverse reactions attributed to the vaccine’.^18^ Hypersensitivity to the vaccine is extremely unlikely given the constituents present in the vaccine preparation but there may be unforeseeable side effects. A study doctor will check participants postvaccination symptoms daily in relation to the individual and trial stopping rules (online supplemental material 9).

10.1136/bmjopen-2022-068966.supp9Supplementary data

#### Challenge

Some study participants will develop symptomatic paratyphoid infection following challenge, for which risks include development of severe disease or complications. These risks will be greatly minimised by daily reviews by a clinical study team member, daily review of e-diary entries, regular safety bloods and early treatment with an effective antimicrobial. A previous challenge study using the same strain of *S*. Paratyphi A at OVG has demonstrated a good safety profile.^15^

#### Carriage

The likelihood of developing chronic carriage is extremely low in the challenge setting. Participants are treated with ciprofloxacin, a fluoroquinolone antibiotic which is the preferred class of antibiotics for prevention of chronic carriage.^24^ To ensure clearance of infection and to exclude chronic carriage, stool samples for culture will be obtained on completion of the initial antibiotic course. If participants remain positive after a second course of antibiotic treatment then participants will be referred to an Infectious Diseases Consultant at the Oxford University Hospitals NHS Foundation Trust for further management.

#### Close contacts

In view of the low infectivity of *S*. Paratyphi A without bicarbonate buffer and the high standard of hygiene and sanitation in the UK, secondary transmission of the challenge strain to household or other close contacts after discharge is highly unlikely. It is thought that typhoidal Salmonellas, unlike *Shigella* sp, enterohaemorrhagic *Escherichia coli*, or hepatitis A virus, are virtually never transmitted by direct faecal–oral contact. This is in part due to the higher oral inoculum of these bacteria required to cause clinical disease.

It is acknowledged, however, that transmission within households can occur if the individual excreting *S*. Paratyphi A fails to practice effective hand washing after defecation and is subsequently involved in uncooked food preparation. Therefore, throughout the period of possible excretion of the challenge strain, participants must practice stringent hand washing techniques after defecation. Participants will be given soap and paper towels for use at home and detailed advice on how to prevent transmission of *S*. Paratyphi A. Participants will be taught and observed practising good hand hygiene technique at their initial challenge visit.

### AE reporting

All AEs occurring from enrolment to day 28 postchallenge will be recorded and graded (online supplemental material 10). Solicited AEs will be recorded and graded (0–4) by the participant in a vaccine e-diary for 7 days postvaccination and a challenge e-diary 21 days postchallenge. Solicited AEs will be reviewed daily during the periods of recording by a study clinician and if they have concerns about the severity or frequency of an event this will be followed up with the participant. Unsolicited AEs will be recorded by the participant in the e-diaries any time from first vaccine administration until day 28 postchallenge.

10.1136/bmjopen-2022-068966.supp10Supplementary data

All solicited AEs recorded in the e-diary will be automatically assumed to be related to the vaccine or challenge (depending on whether recorded in vaccine diary or challenge diary, respectively) whereas all unsolicited AEs will undergo causality assessment by a clinician as to whether related to the vaccine, challenge agent or other medications.

Laboratory results and vital signs will be entered directly into an eCRF and automatically severity graded. Any clinically significant results will be reported as AEs and causality assessed.

Medically attended non-SAEs occurring between day 28 and day 90 elicited at the day 90 visit will not receive a causality assessment. All SAEs will be recorded from time of consent and reported to the DSMC within 24 hours of notification. SAEs will receive a causality assessment throughout the study, at the time of reporting. All SAEs at least possibly related to CVD 1902 will be considered unexpected and be reported to the MHRA and REC as serious unexpected serious adverse reactions within the regulatory timelines. AEs of special interest are listed in box 4. These will be reported to the DSMC as soon as possible but within 7 days of discovery.

Box 4Adverse events of special interest in the Vaccine against *Salmonella* Paratyphi A trialAdverse events of special interestSevere paratyphoid infection.*Failure to clinically or bacteriologically cure a participant of paratyphoid infection.Progression to chronic carrier state.Relapse of paratyphoid infection.Transmission of *Salmonella* Paratyphi A to a contact of a participant.AEs requiring a physician visit or emergency department visit which, in opinion of study staff, are related to challenge with *S*. Paratyphi A.Pregnancy.*Severe paratyphoid infection defined as illness that includes any of the following criteria: oral temperature >40°C, systolic blood pressure <85 mm Hg, significant lethargy or confusion, gastrointestinal bleeding, gastrointestinal perforation or any grade 4 or above laboratory abnormality.

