**Methods and analysis:**

This is an observer-blind, randomised, placebo-controlled trial phase I/II of the oral live-attenuated vaccine against *S*. Paratyphi A, CVD 1902. Volunteers will be randomised 1:1 to receive two doses of CVD 1902 or placebo, 14 days apart. One month following second vaccination all volunteers will ingest *S*. Paratyphi A bacteria with a bicarbonate buffer solution. They will be reviewed daily in the following 14 days and diagnosed with paratyphoid infection if the predefined microbiological or clinical diagnostic criteria are met. All participants will be treated with antibiotics on diagnosis, or at day 14 postchallenge if not diagnosed. The vaccine efficacy will be determined by comparing the relative attack rate, that is, the proportion of those diagnosed with paratyphoid infection, in the vaccine and placebo groups.

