#### Challenge visits

*S*. Paratyphi A challenge will be administered by the oral route following pretreatment with sodium bicarbonate solution. Participants will be directly observed for 15 min following challenge and if they vomit within 60 min of challenge will be treated with antibiotics and withdrawn from the study.

Following challenge administration participants will be seen daily for 14 days and instructed to complete an online challenge e-diary to record oral temperatures two times a day and to describe any symptoms or the use of any medications for 28 days (online supplemental material 6).

10.1136/bmjopen-2022-068966.supp6Supplementary data

Paratyphoid infection will be diagnosed based on certain prespecified criteria as seen in box 3.

Box 3Criteria for diagnosis of paratyphoid following human challengeParatyphoid fever is diagnosed if any of the following applyA positive blood culture for *Salmonella* Paratyphi A from 72 hours postchallenge.A positive blood culture for *S.* Paratyphi A within 72 hours postchallenge, with one or more signs/symptoms of paratyphoid infection (such as recorded temperature ≥38.0°C).Persistent positive blood cultures (two or more blood cultures taken at least 4 hours hours apart) for *S.* Paratyphi A within 72 hours postchallenge.Oral temperature ≥38.0°C persisting for 12 hours in the 14 days following challenge.

Once diagnosed, participants are treated with antibiotics and monitored for severity of infection. Participants will be provided with medications for symptomatic control if required. At any stage, if clinically indicated, an additional review will be arranged by the clinical study team or if severely unwell they will be directed to the local accident and emergency department (or appropriate other medical facility) and relevant medical personnel from the trial and secondary care will be made aware. Antibiotics may also be started if felt to be clinically necessary or participant has severe symptoms not meeting diagnostic criteria.

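### Solicited symptoms in the 21-day challenge diary are labelled challenge-related by rule, although every challenged participant is scheduled to take antibiotics inside that window

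*Protocol article*

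**What the plan says.** All of the following is in the protocol article.

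- **Attribution of solicited events** (AE reporting): "All solicited AEs recorded in the e-diary will be automatically assumed to be related to the vaccine or challenge", according to which diary the entry is in. For the challenge diary that means challenge.
- **Attribution of unsolicited events** (same sentence): "all unsolicited AEs will undergo causality assessment by a clinician as to whether related to the vaccine, challenge agent or other medications".
- **Window** (AE reporting): solicited events are graded in "a challenge e-diary 21 days postchallenge". The Challenge visits section gives the diary a longer span and tells participants "to describe any symptoms or the use of any medications for 28 days".
- **Who takes antibiotics** (Abstract, Methods and analysis): "All participants will be treated with antibiotics on diagnosis, or at day 14 postchallenge if not diagnosed". The Antibiotics section agrees.
- **Length of course** (Antibiotics): "The first line antibiotic will be oral ciprofloxacin 500 mg two times a day for 7 days". The same section says participants will be told about possible side effects of this drug.
- **Clinician review** (AE reporting): solicited entries are reviewed daily, and follow-up is triggered by concern about how severe or how frequent an event is. Cause is not mentioned.

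**The concern.** Assuming relatedness is easy to defend in the 7-day vaccine diary, where no other active agent is scheduled. The challenge diary is different, because the plan itself gives everyone a second agent with acknowledged side effects during the recording period. For an unsolicited event on day 16 a clinician may name the antibiotic as the cause. For a solicited event on the same day the rule leaves no such option.

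Two things are at stake. The challenge-related symptom profile would mix infection with treatment effects, in a model the authors expect to be used for other vaccine candidates (Discussion). And if those labelled events are used for secondary objective (a) in Table 1, which compares the clinical course after challenge between arms, some of what is compared would be antibiotic tolerability.

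**Working it through.** **1. Does the course fall inside the window?** The latest scheduled start is day 14. A 7-day course covers days 14 to 20, or finishes on day 21 if the first dose is late on day 14. Earlier diagnosis moves the course earlier. The first-line course therefore fits in the 21-day window, and also in the 28 days given under Challenge visits. Lengths of second-line courses are not stated.

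**2. The plan's own figure.** The attack rates come from Sample size: 58% placebo and 58% × 0.30 = 17.4% vaccine. With 90% power and two-sided 5%, the usual two-proportion formula gives 28 per group without continuity correction and 33 with it. The stated 33 is thus reproduced, and the attack rates can be used as they stand. Inflation for dropout gives 37–38 per group.

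**3. Exposure by arm.** Expected antibiotic days per participant = AR × 7 + (1 − AR) × 7.

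- Placebo: 0.58 × 7 + 0.42 × 7 = 7.0
- Vaccine: 0.174 × 7 + 0.826 × 7 = 7.0

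Totals are equal. Timing is not. The day of diagnosis is not given, so I assume it:

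| Assumed diagnosis day | Before day 14, placebo / vaccine | From day 14, placebo / vaccine |
|---|---|---|
| 4 to 7 | 4.06 / 1.22 | 2.94 / 5.78 |
| 10 | 2.32 / 0.70 | 4.68 / 6.30 |

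**4. Who takes the course without diagnosed infection?** The share is 1 − AR: 82.6% vaccine, 42% placebo. With 38 per arm that is 38 × 0.826 = 31.4 and 38 × 0.42 = 16.0. With 33 per arm it is 27.3 and 13.9.

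**5. When does this become a difference between arms?** Let *a* be the chance that the antibiotic causes a solicited symptom, taken as equal in everyone. Let *s1* and *s0* be the proportions of diagnosed and undiagnosed participants who report a solicited symptom in the window anyway, taken as equal across arms and independent of *a*. The antibiotic then creates a new participant with a challenge-related symptom with probability

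*a* × [AR × (1 − *s1*) + (1 − AR) × (1 − *s0*)].

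Vaccine minus placebo is *a* × (*s1* − *s0*) × (0.58 − 0.174) = 0.406 × *a* × (*s1* − *s0*). With 38 per arm and *a* = 10% (an assumption; range 5–20%):

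- *s1* = *s0*: no difference.
- *s1* = 1 and *s0* = 0, the extreme case: 38 × 0.406 × 0.10 = 1.5 participants (range 0.8 to 3.1).

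The documents give none of *a*, *s1* and *s0*. If events rather than participants are counted, the extra number is the same in both arms: 38 × 0.10 = 3.8 and 3.8.

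**The case against.** The strongest case against has four parts.

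- **No imbalance in exposure.** A reader might infer from the 31 versus 16 undiagnosed participants that mislabelling is about twice as common in the vaccine arm. The documents do not support that. Those counts leave out the diagnosed participants (38 × 0.174 = 6.6 vaccine, 38 × 0.58 = 22.0 placebo), whose antibiotic symptoms fall under the same rule. Over everyone, exposure is equal. This part stands, and it leaves only the smaller participant-level effect in step 5 of the working.
- **The link to objective (a) is not stated.** Its outcome draws on clinical reporting, examination, microbiology and laboratory assays, and does not mention causality labels. If the comparison is limited to participants with paratyphoid infection, the undiagnosed do not enter it. This stands too, so the effect on objective (a) is only possible.
- **The overlap cannot be checked.** The solicited symptom list is in a supplement that is not shown. This stands as a limit on size. It does not remove the problem with the rule.
- **A uniform rule is conservative and simple.** It avoids asking clinicians to separate resolving infection from drug effect symptom by symptom. That is a fair reason to keep such judgements optional. It is no reason to report a symptom that began during the antibiotic course as due to challenge alone. The diary already records medication use, so the analysis could separate the periods, but the prespecified label would still name only challenge.

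**Conclusion.** The concern holds in a limited form. Followed as written, the rule labels as challenge-related any antibiotic side effect that is also a solicited symptom, and every challenged participant on schedule is exposed to this. That rests on stated text and on the dates alone.

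A difference between arms is a weaker inference. It requires that diagnosed participants report solicited symptoms more often than undiagnosed ones (*s1* > *s0*), that participants rather than events are counted, and that the design attack rates are roughly right. If so, the vaccine arm's count is inflated somewhat more and its apparent clinical benefit shrinks. The documents do not allow the size to be fixed. Under the assumed 5–20% side-effect rate it is at most about 1 to 3 participants of 38. The Discussion expects some diagnoses to be subclinical bacteraemia, which puts *s1* below 1 and the effect below that ceiling.

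The primary endpoint rests on blood culture and temperature and is untouched. Serious events, unsolicited events and clinically significant laboratory or vital-sign results still receive a causality assessment. This is a worthwhile correction to AE reporting and no threat to the trial's main conclusion.

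**What to change.** 1. In AE reporting, restrict the automatic challenge-related label to solicited symptoms with onset before the first antibiotic dose.
2. Label solicited symptoms with later onset as challenge or antibiotic. Optionally, apply to them the causality assessment already used for unsolicited events.
3. Tabulate solicited post-challenge events by arm separately before and after antibiotic start, using the medication data the diary already collects.

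Keep the whole-window table by randomised arm beside the split one. Antibiotic start depends on diagnosis, so time before antibiotics differs by arm. With diagnosis assumed on day 7, it averages 0.58 × 7 + 0.42 × 14 = 9.9 days for placebo and 0.174 × 7 + 0.826 × 14 = 12.8 days for vaccine. The split tables should be read as descriptive, with days of observation shown.

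The cost is a wording change, one derived flag, one extra table and a less simple label during the antibiotic week. The optional causality assessment would add clinician judgements. Treatment of participants does not change.

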#### Follow-up visits

Participants will be followed up for 365 days following challenge. To detect chronic carriage of *S*. Paratyphi A and to confirm clearance, all participants are required to produce three stool samples obtained a minimum of 48 hours apart produced at least 1 week after completion of the antibiotic course. Participants with three successive negative stool samples will be considered to be fully treated for *S*. Paratyphi A infection and no longer an infection risk. The participants GP and local Health Protection Unit will be notified following challenge with *S*. Paratyphi A and then again once the participant has completed their clearance samples.

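### Non-serious medical attendances from day 28 to day 90, elicited at day 90, get no causality assessment, so no stated route leads them to the challenge-related AESI in Box 4

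*Protocol article*

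**What the plan says.** All the relevant rules are in the AE reporting section of the protocol article and its Box 4.

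- General recording has an end date: "All AEs occurring from enrolment to day 28 postchallenge will be recorded and graded".
- Within the e-diary period, which also closes at day 28 after challenge, "all unsolicited AEs will undergo causality assessment by a clinician as to whether related to the vaccine, challenge agent or other medications".
- After that, for non-serious events: "Medically attended non-SAEs occurring between day 28 and day 90 elicited at the day 90 visit will not receive a causality assessment".
- Serious events are handled separately and without an end date: "All SAEs will be recorded from time of consent and reported to the DSMC within 24 hours of notification", and "SAEs will receive a causality assessment throughout the study, at the time of reporting".
- Box 4 lists seven AESIs. One of them is "AEs requiring a physician visit or emergency department visit which, in opinion of study staff, are related to challenge with" *S*. Paratyphi A. Neither the box nor the text around it limits this item in time.
- On AESI reporting: "These will be reported to the DSMC as soon as possible but within 7 days of discovery".

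The Follow-up visits section sets total follow-up at 365 days after challenge.

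**The concern.** The Box 4 item on medical attendance depends on relatedness. An attendance alone does not qualify; someone on the study team has to consider it linked to the challenge. The AE reporting text removes the causality assessment from non-serious attendances elicited at day 90. A team could follow that text to the letter and never form the opinion that Box 4 asks for.

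This item also works as the catch-all among the AESIs. It picks up challenge-related illness that took a participant to a doctor without meeting the definition of severe infection, relapse, failed cure or carriage. Suppose a participant sees a doctor at day 40 with a non-serious complaint of that kind and mentions it at the day 90 visit. It would be recorded as an attendance with no attribution, and nothing in the text would prompt a report to the DSMC. At stake is whether the DSMC's view and the final account of late challenge safety include such events.

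**Working it through.** The plan gives no figure to reproduce. The check sets the rules side by side.

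1. **Events excluded from causality assessment.** Three conditions apply together: the event is non-serious, it was medically attended between day 28 and day 90, and it is elicited at the day 90 visit. The window is 90 − 28 = 62 days.

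2. **Events in the Box 4 item.** Three conditions apply together: it is an adverse event, it required a doctor or emergency department, and study staff consider it related to challenge. There is no time limit.

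3. **Overlap.** A non-serious doctor or emergency department attendance in the 62-day window, elicited at day 90, meets the first two Box 4 conditions. Only relatedness remains open, and that is the assessment the AE reporting text withholds. The two rules therefore act on the same events and point in opposite directions.

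4. **Is there another stated route?** The AE reporting section offers three to consider.
   - The clinician assessment of unsolicited events belongs to e-diary recording, which ends at day 28, before the window.
   - The assessment that runs throughout the study covers serious events only.
   - The day 90 visit is the only stated point at which non-serious attendances after day 28 are collected, and it is the one that carries the exclusion.

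   So the article states no other route.

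5. **What is outside the conflict.** Serious events are assessed and reported throughout. Of the seven Box 4 items, 7 − 1 = 6 need no causality judgement on an attendance: severe infection, failure to cure, chronic carriage, relapse, transmission to a contact, and pregnancy. These stay reportable under the 7-day rule whenever they are discovered.

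6. **Size.** The affected set is one of seven AESI items over 62 days, limited to non-serious events elicited at day 90 that meet no other Box 4 item. The article gives no expected rate of such events. The length of the window says nothing about how many would occur, so no count can be derived.

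**The case against.** The best defence is that Box 4 asks only for the opinion of study staff, which is less than a formal causality grading. Staff could hold and report that opinion without completing an assessment, and an event they hear of before the day 90 visit is not clearly caught by the exclusion. This is a fair reading. It rules out saying that these events cannot reach the DSMC. It does not settle the conflict, because the article does not say that an informal opinion counts once the formal assessment has been withdrawn, and two clinicians could act differently while both comply.

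A reader might also infer that relapse, failed cure and carriage go unreported, since clearance needs "three stool samples obtained a minimum of 48 hours apart produced at least 1 week after completion of the antibiotic course" and can run past day 28. The documents do not support that. Each of those is its own Box 4 item with no relatedness condition, and clearance sampling is a study procedure required of all participants, not a medical attendance.

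Nor does the text show that AESI collection stops at day 28. That date bounds general adverse event recording; Box 4 has no end date.

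Finally, the article condenses protocol version 3.1 and refers to supplements on visits and on adverse event grading that are not shown. They may give an AESI window or a day 90 procedure. That limits confidence about how the trial is run in practice. The conflict between two explicit statements in the article remains.

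**Conclusion.** The point holds in a narrow form. For non-serious medical attendances between day 28 and day 90 that are elicited at the day 90 visit, the AE reporting text and Box 4 contradict each other, and the plan has no stated route by which such an event becomes the challenge-related AESI. Late non-serious challenge-related events may be under-counted as a result.

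It would be tempting to conclude that the reported safety profile is biased towards no late harm. The documents do not show this. The attendances are still elicited, nothing says that only events labelled related will be presented, and a comparison by randomised group needs no causality field.

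The conclusion assumes that the unseen full protocol and supplements do not already resolve the matter, and that staff would read the exclusion as covering the opinion Box 4 calls for.

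**What to change.** Reconcile the two statements by amending the AE reporting text along these lines: non-serious medically attended events from day 28 to day 90 will be judged for relatedness to challenge when they become known, at the latest at the day 90 visit, and any judged related will be handled as AESIs and reported to the DSMC under the existing 7-day rule. State in Box 4, or beside it, the period over which this item applies, so that staff know whether it ends at day 90 or continues through follow-up to day 365.

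In practice this needs one relatedness-to-challenge field on the day 90 form and a sentence of protocol wording. The downside is a clinician's judgement on what should be a small number of events. Since the plan is for every participant to be challenged, the question asked is the same in both groups. No change to sample size, visits or the efficacy analysis follows.
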